### Study Implementation Plan

This study will be implemented in collaboration with the district health system. As per randomization of the study arms, the existing mechanisms of VHNSC, women’s SHGs, and schools would be utilized for study implementation by using the principles of participatory development in a phased manner as depicted in Figure 1 and as described below.

**Figure 1 figure1:**
[figure not shown]
Study flowchart showing the phases and respective activities. FGD: focus group discussion; IEC: institutional ethics committee; MSRLM: Maharashtra State Rural Livelihood Mission; NCD: noncommunicable disease; NP-NCD: National Programme for Prevention & Control of Non-Communicable Diseases; PHC: primary health center; SHG: self-help group; VHNSC: Village Health Nutrition and Sanitation Committee.

#### Phase 1: Preparatory Phase (6 Months)

The preparatory phase will include liaising and seeking administrative approvals, staff recruitment, baseline data collection, and a formative study for developing the health promotion module.

##### Liaising and Seeking Administrative Approvals (First Month)

The preparatory phase will include seeking approval from the institutional ethics committee and concerned district authorities from health, education, zilla parishad, and livelihood mission departments. Piloting of data collection tools and planning for baseline data collection will be performed.

##### Baseline Data Collection (Second Month to Fourth Month)

A baseline assessment of the prevalence of NCD-related modifiable risk factors, that is, obesity, addiction, stress, and dietary practices, including salt consumption, physical activity, and hypertension or prehypertension will be conducted using the STEPS approach developed by the World Health Organization (WHO) [27]. The study questionnaires will include sociodemographic details, NCD risk factor survey, stress questionnaire, anthropometry, and blood pressure measurements. The details of these tools are given in a later section. Sample size was estimated separately for behavioral and biochemical risk factors by using G*power software (version 3.1; Institute for Experimental Psychology) for behavioral as well as biochemical risk factors.

##### Sample Size for Behavioral Risk Factors

We hypothesize that our interventions would reduce the modifiable behavioral risk factors for NCDs by 25% over a period of 3 years. With an assumption of the lowest prevalence of NCD-related risk factors at 13% [6-8,28,29] to detect the aforesaid difference, with 95% CIs, power of 80%, intracluster correlation coefficient of 2, an approximate sample of 12,000 participants, that is, 3000 in each arm, was calculated. Sample size was estimated using the lowest risk factor prevalence, as it gives the maximum possible sample size. We will utilize stratified random sampling (stratified by gender) to select the study participants. The sampling frame will be prepared from the already existing health and demographic surveillance system, which is established by the Department of Community Medicine, Mahatma Gandhi Institute of Medical Sciences, in 5 PHCs (including the study PHCs) covering around 113 villages and a population of about 120,000 people. The health and demographic surveillance system is updated every 6-12 months, and data from the most recent round will be used for the abovementioned purpose.

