## Introduction

### Background

Low- and middle-income countries such as India are facing the emerging burden of chronic noncommunicable diseases (NCDs) while still struggling with the unfinished agenda of improving maternal and child health, nutrition, and infectious disease spread [1]. The burden of cardiovascular diseases, chronic respiratory diseases, diabetes, cancer, and mental disorders is predicted to increase significantly in the next 25 years [1]. NCDs are estimated to account for about 75% of all deaths in India by 2030 [1]. Cancer deaths are projected to double from 2004 to 2030, and cardiovascular disease deaths are predicted to increase from 2.7 million in 2004 to 4 million in 2030 [1]. Apart from high costs to the health system, NCDs result in high out-of-pocket expenditure. The overall economic burden of NCDs in India is estimated to amount to approximately 5%-10% of the gross domestic productivity, thus imposing huge social and economic costs, impeding not only health improvements but also economic progress and social development of the country [2]. Evidence suggests that NCDs disproportionately impact people at younger ages and are increasingly afflicting the poorer segments of the society [2,3].

The National Family Health Survey has shown that throughout India, over 10% of the population aged 15 years and older have elevated blood sugar levels and over 20% of the population have elevated blood pressure levels [4,5]. Various studies [6-9] have highlighted the need of early interventions for the primary and secondary prevention of NCD-related risk factors. For instance, a study in Central India reported that the prevalence of hypertension was 5.75% among adolescents, which highlights the need for blood pressure and nutritional monitoring among adolescents [6]. Overweight or obesity has been reported in 4.3% of schoolchildren in Wardha, with a dietary deficiency in 57% of the adolescent girls [7]. Metabolic syndrome (clustering of abdominal obesity, hypertension, disturbed glucose metabolism, and dyslipidemia) has been reported in 9.3% of the rural adult population in India [8]. A recent review from low- and middle-income countries highlights the role of community-based interventions through health-promotion initiatives in reducing the risk factors related to NCDs. Such interventions significantly reduce the risks ranging from lifestyle and diet modifications, smoking, alcohol, etc [9].

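### Two inputs of the behavioural sample size are wrong as printed: an intracluster correlation of 2 is impossible, and 13% is not the lowest prevalence among the protocol's own cited figures.

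*Protocol article*

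**What the plan says.** The section Sample Size for Behavioral Risk Factors expects the interventions to "reduce the modifiable behavioral risk factors for NCDs by 25% over a period of 3 years". It continues: "With an assumption of the lowest prevalence of NCD-related risk factors at 13% [6-8,28,29] to detect the aforesaid difference". The remaining inputs are "with 95% CIs, power of 80%, intracluster correlation coefficient of 2", and the result is "an approximate sample of 12,000 participants, that is, 3000 in each arm, was calculated". The choice of 13% is then justified: "Sample size was estimated using the lowest risk factor prevalence, as it gives the maximum possible sample size".

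The Background reports, from two of the references cited for the 13%, that "the prevalence of hypertension was 5.75% among adolescents" (reference 6) and that "Overweight or obesity has been reported in 4.3% of schoolchildren in Wardha" (reference 7).

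Both conditions belong to this survey. The closing paragraph of the Background lists overweight or obesity and high blood pressure among the target risk factors. Baseline Data Collection includes obesity and hypertension or prehypertension in the assessment of NCD-related modifiable risk factors. Data Collection Tools states that everything except the biochemical tests is measured on all 12,000 participants.

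**The concern.** There are two separate faults in one paragraph.

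(a) A correlation of 2 does not exist. Either the quantity is mislabelled or the calculation is wrong, and the printed text does not show which. An intracluster correlation and a design effect are linked through the cluster size, so until the 2 is identified nobody can judge whether the allowance for clustering is reasonable.

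(b) The argument for 13% is that the rarest factor needs the most people, so sizing on it gives the largest sample. For a fixed relative reduction that logic is right, but it works only if 13% really is the lowest prevalence. The protocol's own Background gives lower values from the same references, for conditions measured in the same survey.

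At stake is how results will be read. If overweight or hypertension shows no effect, a reader who relies on this paragraph may believe the survey had been sized to detect a 25% reduction in those outcomes too.

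**Working it through.** **Inputs.** From the sample size section: baseline 13%, a 25% reduction (read as relative, so 9.75%), 95% confidence (taken as two-sided 5%; sidedness is not stated), 80% power, a clustering input of 2, and 3000 per arm. From the Background: 4.3% and 5.75%.

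**Formula.** Two independent proportions, pooled variance under the null, no continuity correction:

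n = [1.96·√(2p̄(1−p̄)) + 0.8416·√(p₁(1−p₁) + p₂(1−p₂))]² / (p₁−p₂)²

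**Step 1: reproduce the plan's figure.** p₁ = 0.13, p₂ = 0.0975, p̄ = 0.11375, difference 0.0325.
- √(2 × 0.11375 × 0.88625) = 0.4490
- √(0.13 × 0.87 + 0.0975 × 0.9025) = 0.4484
- n = (1.96 × 0.4490 + 0.8416 × 0.4484)² / 0.0325² ≈ 1497 per arm
- Multiplied by 2: 2994 per arm, 11,976 over four arms, which agrees with 3000 and 12,000.

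Unpooled variance (1495) and the arcsine method (1492) lead to the same place. A one-sided test gives 1180, or 2360 doubled, which does not match.

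**Step 2: try 2 as a correlation.** Design effect = 1 + (m − 1) × ICC. With ICC = 2 it is 1 + 2999 × 2 = 5999 for m = 3000, and 1 + 119 × 2 = 239 for m = 120. Neither leads to 3000 per arm. Only a design effect of 2 does.

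**Step 3: what a design effect of 2 could mean.** The article gives no cluster size for this calculation. As an assumption, splitting about 100 villages equally over 4 arms gives 25 per arm and 3000 / 25 = 120 respondents per village. If the village were the cluster, ICC = (2 − 1) / (120 − 1) = 0.0084. This is an illustration only; the authors alone know what the 2 stood for.

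**Step 4: apply the paragraph's own rule to the lower figures.** Same formula, 25% relative reduction, design effect 2. Power is Φ[((p₁−p₂)·√1500 − 1.96·√(2p̄(1−p̄))) / √(p₁(1−p₁)+p₂(1−p₂))], with effective n = 3000 / 2 = 1500 per arm.

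| Baseline | After 25% reduction | n per arm, unclustered | n per arm × 2 | Power at 3000 per arm |
|---|---|---|---|---|
| 13% | 9.75% | 1497 | 2994 | 80% |
| 5.75% | 4.3125% | 3629 | 7257 | 44% |
| 4.3% | 3.225% | 4917 | 9835 | 34% |

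(Doubling is done before rounding.) For example, at 4.3%: (0.01075 × 38.73 − 1.96 × 0.2691) / 0.2690 = −0.41, and Φ(−0.41) = 0.34. By the rule the paragraph states, the lowest cited figure would call for 9835 / 3000 = 3.3 times the planned number per arm.

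**The case against.** The best defence of the 2 is that it is a slip in a term. Read as a design effect it reproduces the sample size, so nothing numerical changes. That stands: part (a) is a labelling error. A condensed article may also leave the ICC and cluster size to the full protocol, but it cannot print an impossible value in their place.

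The best defence of the 13% is the section heading and hypothesis, which speak of behavioural factors. Overweight and hypertension are not behaviours, Table 3 lists both as secondary, and 13% may be the lowest strictly behavioural prevalence, perhaps from references 28 and 29, whose figures the article does not give. That is possible and cannot be checked. It does not rescue the sentence as printed, which speaks of NCD-related risk factors, the term Baseline Data Collection uses for a set that includes obesity and hypertension, and which cites references 6 to 8. The Statistical Analysis Plan also makes the prevalence of various modifiable risk factors primary, without restriction to behaviours.

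The lower figures have limits too. The 4.3% is from schoolchildren and the 5.75% from adolescents, while the survey covers ages 10 to 30. The planned blood pressure measure is hypertension or prehypertension, which must be at least as common as hypertension alone, and the Background gives over 20% with elevated blood pressure at age 15 and above. This caveat stands and makes the lower powers illustrative.

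A reader might infer more than the document supports:
- That the protocol promises 80% power for every risk factor. It does not say so; that is at most an inference from the maximum-sample-size sentence.
- That hypertension is shown to be underpowered. It is not, for the reasons just given.
- That the 9.3% for metabolic syndrome, from reference 8, belongs in the table. It is an adult composite and not a listed outcome.
- That the plan assumed a village-level ICC of 0.008. The article states no such value.

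Whether one health centre per arm can support the comparison, and what power the difference-in-differences contrast has, are separate questions that do not bear on these two inputs.

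**Conclusion.** The point holds in this form. The intracluster correlation of 2 is impossible, and the evident meaning is a design effect of 2, which leaves 3000 per arm intact. The statement that 13% is the lowest prevalence, and therefore gives the largest sample, is contradicted by figures the same article takes from the same references for conditions measured in the same survey. The stated 80% power applies to factors with a prevalence of about 13% or more. Below that it falls, to about 44% at 5.75% and 34% at 4.3%.

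These powers assume a two-sided 5% test between two arms at one time point, a 25% relative reduction, and a design effect of 2. They show the direction and scale of the loss; they do not forecast power for overweight or hypertension across ages 10 to 30, whose prevalence in that range the article does not give.

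**What to change.** Restate the sample size paragraph, leaving the number of participants as it is:

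1. Replace the intracluster correlation of 2 by a design effect of 2, and have the authors state the ICC and the cluster unit it rests on. The village illustration above should not be written in as fact unless it was the actual basis.
2. Either delete the claim that the lowest prevalence was used and gives the maximum sample, or limit the 13% to named behavioural factors with the source for that figure.
3. State that 80% power applies to factors with a prevalence of about 13% or more, and report the lower power for rarer factors such as overweight or obesity, using prevalences for ages 10 to 30 where these are available.

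The cost is one rewritten paragraph and a less favourable power statement for low-prevalence factors.

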Operational definitions of health behaviors and procedures for physical measurements and biochemical assessments will be as per the standard procedures in the WHO-STEPwise tool for the NCD risk factor surveillance. Height and weight will be measured as described in the WHO STEPwise surveillance module. For blood pressure measurements, all the readings will be recorded by trained personnel to reduce the interobserver variation. Training in all relevant techniques will be given, including care for avoiding expectation error and digit preference. The forearm will be kept at the level of the heart. The sphygmomanometer will also be kept at the level of the heart. Two readings of blood pressure will be taken: one at the beginning of the assessment and the second at midway in the assessment. If the first 2 readings differ by more than 5 mm Hg, an additional reading will be taken and the average of the 3 readings will be noted. For blood sugar and lipid profile, 5 mL of fasting venous blood sample will be collected and transferred to the central laboratory of the institute for further processing and reporting [34]. As specified in the methodology earlier, all the measurements would be performed on 12,000 participants, except for biochemical assessments, which will be performed for a random subset of 1600 participants from among the larger cohort of 12,000 participants. However, a separate random sampling will be performed as specified earlier for the endline assessment as well.

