#### Statistical Analysis Plan

The primary outcome variable for this study would be the prevalence of various modifiable NCD risk factors as compared to baseline. Descriptive analysis will be performed using proportions with 95% CIs. For the quantitative information, difference in differences analysis using *Z*-test for differences between proportions of independent samples and ANOVA or multivariate analysis of covariance will be used to find out the effectiveness of the intervention between the intervention and the control groups. Here, the 3 interventions will be evaluated independently to demonstrate the feasibility and efficacy of each of the 3 intervention modalities. In addition, multivariate regression will be performed for finding the determinants of the risk factors, and exploratory factor analysis will be performed to explain the observed variances between intervention and control groups. For the qualitative data, thematic content analysis will be performed.

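### The stated 80% power fits one comparison of two proportions; the difference in differences named for effectiveness has about 49% to 78% at the 13% planning prevalence with independent rounds

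*Protocol article*

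**What the plan says.** The protocol article, under Sample Size for Behavioral Risk Factors, hypothesises that the interventions will "reduce the modifiable behavioral risk factors for NCDs by 25% over a period of 3 years". It takes the "lowest prevalence of NCD-related risk factors at 13" per cent, because the rarest factor demands the largest sample. The remaining inputs and the result are given as "with 95% CIs, power of 80%, intracluster correlation coefficient of 2, an approximate sample of 12,000 participants, that is, 3000 in each arm".

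The Abstract (Results) gives 12,000 people, 3000 per arm, as the number assessed at baseline and again at endline. Data Collection Tools adds that "a separate random sampling will be performed as specified earlier for the endline assessment as well".

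The Statistical Analysis Plan section defines the primary outcome as the prevalence of various modifiable risk factors relative to baseline. For effectiveness it opens with "For the quantitative information, difference in differences analysis using" a Z-test for proportions from independent samples. It then names ANOVA or multivariate analysis of covariance, and says that each of the three interventions is evaluated on its own.

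**The concern.** Sample size, stated power and named analysis should describe the same contrast. The sample-size paragraph has no term for a second survey round. A difference in differences on separately drawn samples subtracts one estimated change from another, so its variance is roughly twice that of a single difference between two proportions. A sample that gives 80% power for the simple difference cannot give 80% for the double difference under the same inputs.

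What is at stake is how a null result would be read. If a low-prevalence factor shows no significant difference in differences, a reader who relies on the stated 80% would take this as fair evidence against a 25% reduction. The actual chance of detecting that reduction would have been lower, possibly much lower. The article also says that its very large sample keeps random error small, which encourages that reading.

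**Working it through.** **Inputs.** From the sample-size section: prevalence 13%; a 25% relative reduction, so 0.13 × 0.75 = 9.75%, a difference of 3.25 points; 95% confidence, read as two-sided 5%; power 80%; a clustering input of 2; 3000 per arm. From the Abstract and Data Collection Tools: 3000 per arm in each round, with a separate draw at endline.

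**Assumption on clustering.** The text gives an "intracluster correlation coefficient of 2". A correlation cannot exceed 1. I read it as a design effect of 2, because that reading reproduces the stated sample.

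**Step 1: reproduce the plan's figure.** For two independent proportions, with mean proportion 0.11375:

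n per group = [1.96 × √(2 × 0.11375 × 0.88625) + 0.842 × √(0.13 × 0.87 + 0.0975 × 0.9025)]² / 0.0325² ≈ 1497.

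Times 2 = 2994, which is the stated 3000 per arm. Conversely, 3000 / 2 = 1500 effective per group gives 80.1% power. A one-sided test would give 1180 × 2 = 2360, which does not fit. The 80% is therefore the power of one two-proportion comparison. The article does not say whether the pair is intervention against control at endline or baseline against endline within an arm; the arithmetic is the same.

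**Step 2: difference in differences, design effect 2 in every cell.** Four independent samples, effective size 1500 each, three cells at 13% and the intervention endline cell at 9.75%:

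- Standard error = √[(3 × 0.1131 + 0.0880) / 1500] = 0.0169, or 1.69 points.
- 3.25 / 1.688 = 1.926.
- Power = Φ(1.926 − 1.96) = 48.6%. A simulation with 200,000 replicates also gave 48.6%.

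**Step 3: cluster effects that cancel between rounds.** If the same places are surveyed twice, stable differences between them drop out of a difference in differences, which lowers the effective design effect. The values below 2 are assumptions.

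| Design effect | Power at 13% prevalence |
|---|---|
| 2 | 49% |
| 1.5 | 60% |
| 1.2 | 70% |
| 1 (complete cancellation) | 78% |

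**Step 4: people sampled in both rounds.** With overlap fraction f and within-person correlation ρ, the variance shrinks by roughly (1 − fρ). Neither is given in the article. At design effect 2:

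- f = 0.25, ρ = 0.3: standard error 1.688 × √0.925 = 1.62 points; power 52%.
- f = 0.42, ρ = 0.7: standard error 1.688 × √0.706 = 1.42 points; power 63%.

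**Step 5: other prevalences.** The same method, with a 25% relative reduction and design effect 2, gives 70% at 20% prevalence, 82% at 25% and 90% at 30%.

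**Step 6: what 3000 does deliver at 13%.** At design effect 2, a 36% relative reduction (13.0% to 8.3%) gives 4.68 / 1.664 = 2.81 and power Φ(2.81 − 1.96) = 80%. For comparison only, 80% power for the 25% reduction would need about 3175 effective per cell, or 3175 × 2 = 6350 per arm per round.

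**The case against.** Several points on the other side are fair.

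- **Which comparison the 80% belongs to.** A reader might infer that the sample was sized on an endline contrast between arms. The article does not say so. Its wording about reduction over three years, and an outcome defined relative to baseline, fit a within-arm before-and-after comparison at least as well. Only a single two-proportion comparison can be claimed.
- **49% is the low end.** It applies the full design effect to all four cells, as if cluster effects in the two rounds were unrelated. The same areas are surveyed twice, so some cancellation is plausible. This stands, and it is why a range is given. Overlap of people would help too. Combined with complete cancellation it would pass 80%: f = 0.25 and ρ = 0.3 at design effect 1 give 3.25 / (1.193 × √0.925) = 2.83 and power 81%. The sample-size paragraph invokes neither.
- **The trial as a whole.** A reader might infer that the trial has an even chance of failing. That goes too far. The article chose 13% as its lowest prevalence, and the more common factors are adequately powered by this method.
- **Not the sole primary analysis.** Difference in differences is named first, but ANOVA or multivariate analysis of covariance follows and the Abstract adds regression. No single primary analysis is designated. This limits the point to the first-named method. It does not rescue the figure, because with separate samples most endline respondents would have no baseline value of their own to adjust for.

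It might also be said that a separate analysis plan could settle this. But the point is not an omission: the article itself states a power, a sample size and an analysis that do not fit together.

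**Conclusion.** The concern holds in this limited form. The 3000 per arm matches 80% power for one comparison of 13% with 9.75%, and not for the difference in differences that the article names first. At 13% prevalence that analysis has about 49% power with a design effect of 2 in each cell and about 78% if cluster effects cancel completely. It stays below 80% throughout that range for independent samples.

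The figures rest on these assumptions: the coefficient of 2 is a design effect; the test is two-sided at 5%; control prevalence stays flat; the rounds are independent; the design effect is equal across cells. They also ignore variation between primary health centres, which cannot be estimated with one centre per arm, and they make no allowance for three comparisons with control. Either would lower the real power further; both are separate matters.

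The documents do not support a flat statement that the trial has 49% power, nor one that the 80% was meant for an endline contrast.

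**What to change.** Do not enlarge the trial. Make two changes to the sample-size paragraph.

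1. Replace the correlation coefficient of 2 with the design effect actually used.
2. Restate the power, for example: *The 80% power applies to a single comparison of two independent proportions. For the difference in differences at 13% baseline prevalence, 3000 per arm per round gives about 49% power (design effect 2 in each round) to 78% (cluster effects fully cancelling) for a 25% relative reduction, and 80% power for about a 36% relative reduction at design effect 2. These figures assume flat control prevalence and independent samples, and ignore variance between primary health centres, which cannot be estimated with one centre per arm.*

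The cost is a few sentences and a less favourable stated power. Recruitment and conduct do not change.
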